#### Sensitivity analyses for the primary outcome

We aim to conduct the following sensitivity analyses for the primary outcome to assess consistency and the risk of bias:Evaluation of study intervention effects adjusted by the baseline risk of delirium according to the PRE-DELIRIC score.Evaluation of study intervention effects considering the cluster adherence to FFVM implementation. In this analysis, the study intervention effects will be adjusted by the total fidelity of FFVM implementation score.Evaluation of study intervention effects considering the potential confounding effect of sedation on the delirium diagnosis. In this analysis, the study intervention effects will be evaluated, considering patients with positive CAM-ICU during ICU stay in the context of Richmond Agitation-Sedation Scale (RASS) score – 2 or − 3 as non-delirious subjects.Evaluation of effects of study interventions, considering a best plausible scenario/worst plausible scenario imputation of outcomes among ICUs that did not complete the patient recruitment as follows:*Best plausible scenario*: Imputation of the lowest study cluster/phase incidence of delirium for missing FFVM patients and the highest study cluster/phase incidence of delirium for missing RFVM patients*Worst plausible scenario*: Imputation of the lowest study cluster/phase incidence of delirium for missing RFVM patients and the highest study cluster/phase incidence of delirium for missing FFVM patients.

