## Trial overview

The ICU Visits Study is a cluster-randomized, crossover trial comparing an FFVM (12 consecutive ICU visiting hours per day) with an RFVM (< 4.5 ICU visiting hours per day) in Brazilian adult ICUs. The study background, design, rationale, eligibility criteria, and sample size have been previously published [10]. In brief, mixed adult ICUs of public and private philanthropic hospitals with a restrictive policy of ICU visiting hours (< 4.5 h/day) are randomly assigned to either an FFVM or RFVM in a 1:1 ratio until the recruitment and follow-up of 25 patients (phase 1) (Fig. 1). After a 30-day washout period without subject recruitment, each ICU is switched over to the other visitation model (phase 2) until 25 more patients per site are enrolled and followed. The randomization is stratified by the number of ICU beds (1 to 10 or > 10 ICU beds) and performed using random block sizes of 2, 4, and 6. Consecutive patients aged ≥18 years admitted to the ICU, their closest family members, and bedside ICU professionals in each cluster are considered eligible for the present trial. A complete description of the inclusion and exclusion criteria is shown in Table 1.

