**Fig. 1 Fig1:**
[figure not shown]
Study design. *FFVM* flexible family visitation model, *ICU* intensive care unit, *RFVM* restrictive family visitation model. All ICUs will have a learning period within the first 15 days of phases 1 and 2. During this period, ICUs will receive the intervention (FFVM or RFVM) but will not recruit subjects. Local investigators will use this period to adapt the ICU staff to the organizational aspects of study interventions

**Table 1 Tab1:** Eligibility criteria

	Inclusion criteria	Exclusion criteria
Cluster	Adult medical-surgical ICUs of public and philanthropic hospitals with at least six beds; restrictive policy of ICU visiting hours (< 4.5 h/day)	Structural or organizational impediments to flexible family visitation, according to the Brazilian resolution of minimal operational requirements for ICUs^a^
Patients	ICU patients aged ≥18 years	Coma (RASS − 4 or − 5) lasting > 96 h from the moment of first evaluation for recruitment; delirium at baseline (positive CAM-ICU); cerebral death; aphasia; severe hearing deficit; predicted ICU length of stay < 48 h; exclusive palliative treatment at ICU admission; unavailability of a family member to participate in the flexible family visits; unlikelihood to survive > 24 h; prisoner status; readmission to the ICU after enrollment in the study
Family members	Closest family member of a patient enrolled in the study	Family members who do not speak Portuguese or have serious difficulty in answering the self-applied questionnaires (e.g., due to illiteracy or severe visual or hearing limitations); having another family member already enrolled in the study
ICU professionals	Bedside ICU professionals (physicians, nurses, nursing technicians, and physiotherapists) who assist patients during daytime for at least 20 h/week at the enrolled ICU	ICU professionals who have a planned leave of absence of > 15 days during phase 1 of the study

*CAM-ICU* Confusion Assessment Method for the Intensive Care Unit, *ICU* intensive care unit, *RASS* Richmond Agitation-Sedation Scale

^a^Available from: http://bvsms.saude.gov.br/bvs/saudelegis/anvisa/2010/res0007_24_02_2010.html. Accessed 26 Aug 2017

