### Handling of missing data

We anticipate minimal missing values, given that the study variables will be determined during hospital stay by trained researchers. Nevertheless, the coordinator center will contact site investigators to retrieve any missing data values.

ICUs with incomplete subject recruitment (e.g., less than 50 patients) will be included in the primary analysis for the study outcomes considering all subjects available in the cluster. To assess the risk of bias related to ICUs that did not achieve the patient recruitment goal, multiple imputation techniques will be performed for the primary outcome and presented as sensitivity analyses. The missing values for the variables that compose the HADS, CCFNI, and MBI will be imputed, replacing the missing items with the mean of the answered items in the same subscale, if at least half of that subscale has been answered. The missing values for the variables that compose the PREdiction of DELIRium in ICU patients (PRE-DELIRIC) score will be imputed in a similar way as in the original study [19]. We will assume that if a variable is not determined, most likely the missing variable has a normal or negative value (e.g., no infection, no metabolic acidosis) or a mean value (e.g., Acute Physiology and Chronic Health Evaluation-II [APACHE-II] score) of the study population. We will not perform any imputation for the length of ICU visits per patient per day.

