#### Primary outcome

All the pre-specified study outcomes are described in Table 3. The primary outcome is the cumulative incidence of delirium during ICU stay determined by the CAM-ICU, which was validated for the Brazilian population of critical care patients [21]. The cumulative incidence of delirium is defined as the presence of delirium (at least one positive CAM-ICU score) during the ICU stay. The differences in the incidences of delirium between the FFVM and the RFVM groups will be compared using generalized estimating equations with adjustment for the cluster effect, period effect, and interaction between intervention and period and presented as risk ratio (RR) and 95% CI.

**Table 3 Tab3:** Study outcomes

Outcomes	FFVM	RFVM	Type of effect estimate	Effect estimate (CI)	*p* value^a^
Primary					
Cumulative incidence of delirium:^b^ *n*/total *n* (%)	x/x (xx.x)	x/x (xx.x)	RR	x.xx (x.xx-x.xx)*	x.xx
Secondary					
Patients					
Daily hazard of delirium:^b^ mean (SD)	xx.x (xx.x)	xx.x (xx.x)	HR	x.xx (x.xx-x.xx)**	x.xx
Any ICU-acquired infection:^c^ *n*/total *n* (%)	x/x (xx.x)	x/x (xx.x)	RR	x.xx (x.xx-x.xx)*	x.xx
Proportion of ventilator free-days: mean (SD)	xx.x (xx.x)	xx.x (xx.x)	MD	x.xx (x.xx-x.xx)**	x.xx
ICU length of stay: mean (SD)	xx.x (xx.x)	xx.x (xx.x)	MD	x.xx (x.xx-x.xx)**	x.xx
Hospital mortality: *n*/total *n* (%)	x/x (xx.x)	x/x (xx.x)	RR	x.xx (x.xx-x.xx)**	x.xx
Family members					
HADS anxiety score: mean (SD)	xx.x (xx.x)	xx.x (xx.x)	MD	x.xx (x.xx-x.xx)***	x.xx
HADS depression score: mean (SD)	xx.x (xx.x)	xx.x (xx.x)	MD	x.xx (x.xx-x.xx)***	x.xx
CCFNI satisfaction score: mean (SD)	xx.x (xx.x)	xx.x (xx.x)	MD	x.xx (x.xx-x.xx)***	x.xx
ICU professionals					
Burnout syndrome:^d^ *n*/total *n* (%)	x/x (xx.x)	x/x (xx.x)	PR	x.xx (x.xx-x.xx)*	x.xx
Tertiary					
Patients					
Need for antipsychotic agents: *n*/total *n* (%)	x/x (xx.x)	x/x (xx.x)	RR	x.xx (x.xx-x.xx)*	x.xx
Need for mechanical restraints: *n*/total *n* (%)	x/x (xx.x)	x/x (xx.x)	RR	x.xx (x.xx-x.xx)*	x.xx
Unplanned loss of invasive devices: *n*/total *n* (%)	x/x (xx.x)	x/x (xx.x)	RR	x.xx (x.xx-x.xx)*	x.xx
Proportion of coma-free days: mean (SD)	xx.x (xx.x)	xx. (xx.x)	MD	x.xx (x.xx-x.xx)*	x.xx
ICU-acquired pneumonia:^c^ *n*/total *n* (%)	x/x (xx.x)	x/x (xx.x)	RR	x.xx (x.xx-x.xx)*	x.xx
ICU-acquired UTI:^c^ *n*/total *n* (%)	x/x (xx.x)	x/x (xx.x)	RR	x.xx (x.xx-x.xx)*	x.xx
ICU-acquired BSI:^c^ *n*/total *n* (%)	x/x (xx.x)	x/x (xx.x)	RR	x.xx (x.xx-x.xx)*	x.xx
Family members					

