#### Subgroup analyses for the primary outcome

There will be three a priori defined subgroup analyses for the primary endpoint: (1) effectiveness of the FFVM vs. RFVM in ICUs according to the PRE-DELIRIC score (patients with a predicted risk < 25%, 25–50%, 50–75%, and > 75%); (2) effectiveness of the FFVM vs. RFVM according to patient group (medical vs. surgical and neurocritical vs. non-neurocritical); and (3) effectiveness of the FFVM vs. RFVM in ICUs according to APACHE-II scores (≤15 vs. > 15 points). The consistency of intervention effects across the above-mentioned subgroups will be assessed by means of tests for interaction. The Bonferroni correction will be applied to adjust the subgroup analyses for multiple comparisons.

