#### Secondary outcomes

We will use the following statistical procedures to evaluate the study secondary outcomes:*Daily hazard of delirium*: The daily hazard of delirium will be analyzed using a joint survival model that accounts for the treatment effect (with adjustment for the cluster effect, period effect, and interaction between cluster and period) on repeated daily indicator of delirium within each patient and terminating event (death or discharge from the ICU) [22]. This outcome will be presented as hazard ratio (HR) and 95% CI.*Any ICU-acquired infections*: The differences in the cumulative incidence of any ICU-acquired infection between the FFVM and RFVM groups will be compared using generalized estimating equations with adjustment for the cluster effect, period effect, and interaction between intervention and period. This outcome will be presented as RR and 95% CI.*Ventilator-free days*: The number of ventilator-free days will be evaluated using the 7-day time horizon. Ventilator-free days will be set to 0 for patients who have died. The differences in the mean ventilator-free days between the FFVM and RFVM groups will be compared using generalized estimating equations with adjustment for the cluster effect, period effect, and interaction between intervention and period. This outcome will be presented as mean difference (MD) and 95% CI.*ICU length of stay*: The differences in the mean ICU length of stay between the FFVM and RFVM groups will be compared using generalized estimating equations with adjustment for the cluster effect, period effect, and interaction between intervention and period. This outcome will be presented as MD and 95% CI.*Hospital mortality*: The differences in hospital mortality rates between the FFVM and RFVM groups will be compared using generalized estimating equations with adjustment for the cluster effect, period effect, and interaction between intervention and period. This outcome will be presented as RR and 95% CI.*Symptoms of anxiety and depression among family members*: The differences in the mean HADS scores for anxiety and depression between the FFVM and RFVM groups will be compared using generalized estimating equations with adjustment for the cluster effect, period effect, and interaction between intervention and period. These outcomes will be presented as MD and 95% CI.*Satisfaction among family members*: The differences in the mean CCFNI satisfaction scores between the FFVM and RFVM groups will be compared using generalized estimating equations with adjustment for the cluster effect, period effect, and interaction between intervention and period. This outcome will be presented as MD and 95% CI.*Prevalence of burnout among the ICU professionals*: Burnout is defined as a cumulative MBI score greater than − 9. The differences in the prevalence of burnout between the FFVM and RFVM groups will be compared using generalized estimating equations with adjustment for the cluster effect and baseline MBI total scores. This outcome will be presented as prevalence ratio and 95% CI.

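### The primary delirium risk ratio is not adjusted for PRE-DELIRIC, a collected baseline risk score that enters the effect estimate only in a sensitivity analysis

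*SAP article*

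**What the plan says.** Under Primary outcome, the SAP article compares delirium incidence by "generalized estimating equations with adjustment for the cluster effect, period effect, and interaction between intervention and period and presented as risk ratio (RR"). No patient characteristic appears in that model.

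PRE-DELIRIC has four other roles:
- It is a row of the baseline table (Table 2).
- It has an imputation rule under Handling of missing data: "The missing values for the variables that compose the PREdiction of DELIRium in ICU patients (PRE-DELIRIC) score will be imputed in a similar way". The comparison is with the study that developed the score.
- It defines a subgroup analysis in four bands ("patients with a predicted risk < 25%, 25–50%, 50–75%, and > 75"%).
- It heads the list under Sensitivity analyses for the primary outcome: "Evaluation of study intervention effects adjusted by the baseline risk of delirium according to the PRE-DELIRIC score". That list is introduced as a check of consistency and risk of bias. It does not say which estimate prevails if the adjusted and unadjusted results differ.

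On the design, the Trial overview says that "each ICU is switched over to the other visitation model (phase 2) until 25 more patients per site are enrolled and followed". The legend to Fig. 1 adds a 15-day learning period at the start of each phase, when the assigned model is running and nobody is recruited. Table 1 excludes patients for, among other things, a short predicted stay, poor short-term survival prospects, and "unavailability of a family member to participate in the flexible family visits".

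**The concern.** Randomisation here is of ICUs to an order of visiting models, not of patients. Staff know which model is running when they screen each patient, and several exclusions rest on their judgement. The family-availability exclusion is tied directly to the intervention and could in practice be applied differently when no flexible visits are on offer.

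The crossover removes stable differences between ICUs, and the period term removes a common time trend. Neither removes a difference in patient risk that follows the visiting model within an ICU. A prognostic score measured at patient level can remove the part of that difference that it captures, and it also improves precision. The plan has such a score but leaves it out of the estimate on which the trial will be judged.

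**Working it through.** **Inputs from the SAP article.** 40 ICUs (Discussion and trial status); 25 patients per phase with both models used in every ICU (Trial overview), so 40 × 50 = 2000 patients; result given as an RR with 95% CI (Primary outcome). The article gives no incidence, effect size, intracluster correlation or AUC, so there is no stated figure to reproduce.

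**Assumptions, not in the documents.** Delirium incidence 15%, 20% or 30%; true RR 1.0. On the log-odds scale: between-ICU SD 0.5, ICU-by-period SD 0.2, bed-count effect ±0.3. The score is standard normal with slope d = √2 × Φ⁻¹(AUC) log-odds per SD:
- AUC 0.70: 1.414 × 0.524 = 0.742
- AUC 0.80: 1.414 × 0.842 = 1.190

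These AUC labels are nominal. Generating outcomes this way gives realised AUCs of about 0.68 and 0.77.

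**Precision.** The crossover was simulated 250 times per scenario. Each data set was fitted by log-link Poisson regression with independence working correlation and cluster-robust SE. Terms were treatment and period, with or without the score. The intervention-by-period term was omitted so that a single RR is estimated. Mean SE of log RR:

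| Incidence | Nominal AUC | Unadjusted | With score | Reduction |
|---|---|---|---|---|
| 15% | 0.70 | 0.1072 | 0.1040 | 3.0% |
| 15% | 0.80 | 0.1064 | 0.1000 | 6.0% |
| 20% | 0.70 | 0.0924 | 0.0892 | 3.5% |
| 20% | 0.80 | 0.0906 | 0.0844 | 6.8% |
| 30% | 0.70 | 0.0694 | 0.0666 | 4.0% |
| 30% | 0.80 | 0.0700 | 0.0648 | 7.4% |

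The observed spread of the estimates over the replicates fell by 2–6% (for example 0.0939 to 0.0884 at 20%, AUC 0.80), which is the same order.

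**Bias from a case-mix shift.** Suppose the score is δ SD higher in FFVM patients and visiting has no effect. The expected unadjusted RR is E[expit(a + d(x + δ) + u)] / E[expit(a + dx + u)]. Here x is the score, u collects the ICU-level terms, and a makes the denominator 0.20.

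| δ | Nominal AUC | Direct calculation | Simulated, unadjusted | Simulated, with score |
|---|---|---|---|---|
| 0.1 | 0.70 | 1.053 | 1.053 | 1.002 |
| 0.1 | 0.80 | 1.077 | 1.078 | 1.000 |
| 0.2 | 0.70 | 1.107 | 1.093 | 0.987 |
| 0.2 | 0.80 | 1.158 | 1.160 | 1.000 |

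The 0.987 comes from replicates whose unadjusted RR was also about 1% low (1.093/1.107 = 0.987), so it reflects simulation noise. If the shift fell on the RFVM patients instead, the RR would be the reciprocal: 1/1.053 = 0.95 and 1/1.078 = 0.93 for δ = 0.1, which would look like a benefit of FFVM.

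For scale, at δ = 0.1 the bias is ln(1.053)/0.0912 = 0.57 SE at AUC 0.70 and ln(1.078)/0.0893 = 0.84 SE at AUC 0.80, using the mean unadjusted SEs from those runs.

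**The case against.** The strongest reply is that the plan already contains the adjusted analysis. It is pre-specified, listed first among the sensitivity analyses, and backed by a baseline table that shows the score by arm. A shift that the score captures would be visible to readers. That stands, and it rules out the stronger reading that the plan ignores PRE-DELIRIC. What remains is which estimate carries the conclusion, and the SAP has no rule for the case where the two disagree.

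Second, patients are to be consecutive and the exclusions are worded identically for both models. This lowers the risk of differential recruitment. It does not remove it, because identical wording can still be applied differently by staff who know the model.

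Third, adjustment has a cost. Handling of missing data gives APACHE-II as an example when describing imputation of the score, and Table 2 marks APACHE-II as taken in the first 24 h of inclusion. Part of the score may therefore be recorded under the visiting model already in force. Missing components are set to normal, negative or mean values, and that rule would then feed the headline estimate. These are fair points about how the score is built. They are small beside the gain and can be limited by choosing when components are measured.

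Fourth, the change would come late. The SAP reports 1591 patients enrolled as of March 2018 and says that it does not differ from the protocol. That is a reason to record the change openly. The SAP also says that it was written without knowledge of results, so the choice can still be made blind to the data.

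**Conclusion.** The point holds in a limited form. The headline RR omits a baseline risk score that the trial collects, in a design where case mix can differ between phases of the same ICU. The precision gain from including it is modest: about 3–7% in the SE of log RR under the assumed incidences and AUCs. Protection against bias is the better argument. At 20% incidence, a 0.1 SD shift would put the unadjusted RR at about 1.05–1.08 with no true effect. The size of the shift is hypothetical and the SAP gives no evidence of one. Adjustment removes only what the score captures; the simulation put the whole shift into the score, so its near-complete correction is a best case.

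Two wider readings are not supported:
- A reader might infer that leaving out the bed-count stratum ("The randomization is stratified by the number of ICU beds (1 to 10 or > 10 ICU beds") also costs precision or admits bias in the delirium RR. It does not. Bed count is constant within an ICU that supplies both arms. In the simulation, adding it left the RR unchanged to three decimals and the SE essentially unchanged (0.0924 against 0.0923 at 20%, AUC 0.70).
- A reader might infer that the burnout and staff-satisfaction models lose the within-ICU comparison because they have no period term. A period term does not create that comparison. Both models account for cluster, and burnout already has "adjustment for the cluster effect and baseline MBI total scores".

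**What to change.** Before database lock:
- Add PRE-DELIRIC as a continuous covariate to the primary GEE, with a log link so that the result remains an RR. How the intervention-by-period term is handled is a separate matter that this change does not settle.
- Report the unadjusted RR beside it as the pre-specified sensitivity analysis, and state that the adjusted RR governs.
- Build the score from component values recorded before or at inclusion where available, keep the stated imputation rule, and report how many components were imputed in each arm.
- Record this as a change from the protocol, and amend the SAP section that says there are none.

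The cost is SAP wording and a documented change. No new data are needed, because the score is already planned for the baseline table, the subgroup analysis and the sensitivity analysis.

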**Methods/design:**

The ICU Visits Study is a cluster-randomized crossover trial which compares an FFVM (12 consecutive ICU visiting hours per day) with an RFVM (< 4.5 ICU visiting hours per day) in 40 Brazilian adult ICUs. Participant ICUs are randomly assigned to either an FFVM or RFVM in a 1:1 ratio. After enrollment and follow-up of 25 patients, each ICU is crossed over to the other visitation model, until 25 more patients per site are enrolled and followed. The primary outcome is the cumulative incidence of delirium measured by the Confusion Assessment Method for the ICU. Secondary and tertiary outcomes include relevant measures of effectiveness and safety of ICU visiting policies among patients, family members, and ICU professionals. Herein, we describe all primary statistical procedures that will be used to evaluate the results and perform exploratory and sensitivity analyses of this study. This pre-specified statistical analysis plan was written and submitted without knowledge of the study data.

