#### Adherence to study interventions

The total length of visits per patient per day will be evaluated as the primary adherence variable to the study interventions. We will consider the length of stay of all visitors (whether family members or not) at the bedside of an enrolled patient during the ICU stay. For analytical purposes, we will not consider overlapping visiting hours in the total length of visits per patient per day (i.e., only the period in which there was at least one visitor [apart from the number of visitors] will be considered). The differences in the means of length of visits per patient per day between the FFVM and the RFVM groups will be compared using generalized estimating equations with adjustment for the cluster effect, period effect, and interaction between cluster and period. Additionally, we will describe the FFVM family members’ adherence to the website, and the healthcare professionals’ perception of effectiveness and barriers for implementation of the FFVM.

To assess the fidelity of FFVM implementation, we will perform on-site monitoring visits in all participant ICUs. During these visits, the ICU staff perception about adherence to proposed FFVM processes will be assessed by the coordinating center researchers using semi-structured interviews. During the FFVM period, each ICU will be rated from 0 to 100% (with higher percentages indicating higher levels of adherence to intended FFVM processes) in the following domains: (1) Visiting hours - adherence to visiting hours according to the study protocol; (2) Dissemination - dissemination of the FFVM to family members of ICU patients; (3) Structured meetings - frequency and quality of structured meetings; (4) Staff training - education of the ICU staff about the FFVM procedures. The total fidelity of the FFVM implementation score represents the mean of the four evaluated domains. We plan to perform sensitivity and exploratory analyses considering the effects of FFVM implementation on outcomes.

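### Adjusting the primary risk ratio for a fidelity score that exists only under FFVM does not show whether the effect depends on implementation; a centred intervention-by-fidelity term would

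*SAP article*

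**What the plan says.** Under Adherence to study interventions, fidelity is scored in one arm only: "During the FFVM period, each ICU will be rated from 0 to 100" per cent. The four domains (visiting hours, dissemination, structured meetings, staff training) all describe FFVM processes, and "The total fidelity of the FFVM implementation score represents the mean of the four evaluated domains". No corresponding score is defined for the RFVM phase.

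Under Sensitivity analyses for the primary outcome, the second item has the aim "Evaluation of study intervention effects considering the cluster adherence to FFVM implementation", and its method is that "the study intervention effects will be adjusted by the total fidelity of FFVM implementation score".

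The design is a crossover (Trial overview): "each ICU is switched over to the other visitation model (phase 2) until 25 more patients per site are enrolled and followed". Each ICU therefore supplies patients to both arms, but has a fidelity score from only one of its two phases.

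The plan does not say what value RFVM patients take, whether the score is centred, or which coefficient will be reported.

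**The concern.** The aim is to learn whether the effect on delirium depends on how well an ICU implemented FFVM. That is a question of effect modification. The stated method is covariate adjustment, and its reported result is an adjusted intervention effect. Because the score measures the delivery of one arm, it is not a baseline confounder that adjustment can remove. What the adjusted RR means depends on how RFVM patients are coded, and neither obvious coding makes it answer the question.

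This is the only one of the four listed checks that concerns implementation. An RR that cannot move could be taken as evidence of robustness to poor adherence. An RR extrapolated to zero fidelity could be taken as the effect after allowing for adherence. Neither interpretation would be justified.

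**Working it through.** The plan states no figure on this point, so there is nothing to reproduce. From the SAP article come 40 ICUs, 25 patients per phase, both arms in every ICU, a 0–100 score under FFVM only, and a GEE giving an RR. The fidelity mean and SD are assumptions.

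**Coding A: score = 0 under RFVM, raw scale.** Let T be the 1:1 intervention indicator and F = T × fidelity, with mean μ and SD s under FFVM.

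- Var(T) = 0.25 and Cov(T,F) = 0.25μ.
- Var(F) = 0.5(μ² + s²) − 0.25μ² = 0.25μ² + 0.5s².
- Corr² = μ²/(μ² + 2s²), so VIF = 1 + μ²/(2s²).

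| Assumed mean/SD | Correlation with T | VIF | SE multiplier (√VIF) |
|---|---|---|---|
| 85/10 | 0.99 | 1 + 7225/200 = 37.1 | 6.1 |
| 80/15 | 0.97 | 1 + 6400/450 = 15.2 | 3.9 |
| 70/20 | 0.93 | 1 + 4900/800 = 7.1 | 2.7 |

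Over a wider range (mean 60–90, SD 5–20) the VIF runs from 5.5 to 163. In this model the coefficient of T is the log RR at F = 0, that is, FFVM with zero fidelity.

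**Coding B: the ICU's FFVM score carried to both phases as a main effect.** The score is constant within an ICU, whereas the treatment contrast is within ICU. With balanced phases the two are uncorrelated, so the RR should hardly move. If the cluster effect were fitted as ICU indicators, the score would be fully aliased with them.

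**Coding C: RFVM left missing.** The comparator drops out and there is no RR.

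**Simulation check.** This used 40 ICUs × 2 phases × 25 patients and a log-link Poisson GEE with independence working correlation and robust SEs. Terms were T and period; the intervention-by-period term was left out so that T is one overall effect. There were 150 runs per scenario. Assumptions: RFVM risk 20%, RR 0.8, between-ICU SD 0.25 on the log scale.

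| Scenario | Log RR (SE), no fidelity term | Coding A | Coding B |
|---|---|---|---|
| 80/10, effect unrelated to fidelity | −0.202 (0.094) | −0.150 (0.664) | −0.202 (0.094) |
| 80/10, effect proportional to fidelity | −0.222 (0.094) | −0.052 (0.659) | −0.222 (0.094) |
| As above, 8–25 patients per phase | −0.229 (0.119) | +0.032 (0.823) | −0.229 (0.119) |
| 70/20, effect proportional to fidelity | −0.219 (0.093) | −0.024 (0.309) | −0.220 (0.093) |

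- Coding A, proportional effect: at 80/10 with full recruitment, the typical RR moves from exp(−0.222) = 0.80 to exp(−0.052) = 0.95.
- Coding A, unrelated effect: the shift from −0.202 to −0.150 is about one Monte Carlo standard error (0.647/√150 = 0.053), so there is no evidence of systematic drift. The cost is precision. The 95% limits widen from a factor of exp(1.96 × 0.094) = 1.2 either side to exp(1.96 × 0.66) = 3.6.
- Coding B: the largest change in log RR in any run was 0.005 with full recruitment and 0.016 with unequal recruitment.

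**The case against.** The strongest reply is that coding A is not empty. With RFVM at 0, the covariate equals the product of intervention and fidelity, so its own coefficient is the change in log RR per point of fidelity. This stands. A reader might infer that no version of the planned model carries information on implementation, and the document does not support that. If cluster enters as ICU indicators, coding A coincides with a full interaction model. Without them, the slope compares FFVM patients across ICUs and so mixes effect modification with differences in underlying risk. In either case the plan says it will present the adjusted intervention effect, not this slope.

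Second, the VIFs depend on the origin of the scale. If the FFVM scores are centred at their mean and RFVM is left at 0, T and the covariate are uncorrelated and the VIF is 1 whatever the SD. This also stands. The figures of 7 to 37 describe raw scoring under assumed distributions and are not a general consequence of the plan.

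Third, a reader might infer that the adjusted RR will come out near 1. That is expected only if benefit is roughly proportional to fidelity. Otherwise the estimate is merely imprecise, and its CI would show it.

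Fourth, it can be said that adjustment might loosely mean interaction, or that a condensed article leaves coding to a fuller document. The text points the other way. The item just before uses the same adjustment wording for PRE-DELIRIC, an ordinary baseline covariate, and the subgroup section names interaction tests where effect modification is meant. Coding could be left to another document, but the choice of adjustment as the method is stated here.

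**Conclusion.** The point holds in a limited form. Followed as written, the adjusted RR is either an extrapolation to zero fidelity (RFVM coded 0, raw scale) or practically the primary RR (ICU score in both phases). Neither serves the stated aim of considering cluster adherence.

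Under the first coding the SE inflation is about 2.7- to 6.1-fold for assumed fidelity mean/SD of 70/20 to 85/10. The simulated inflation was somewhat larger: 0.664/0.094 = 7.1 at 80/10, against 5.7 from the formula. Under the second coding the log RR changed by at most 0.016. The sizes rest on assumed fidelity distributions and event rates; the logic of the two codings does not.

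It would be wrong to infer that the trial's main result is at risk. The primary analysis is by intention to treat and does not use the score, no decision rule in the document depends on this check, and visit length is compared separately between arms. The change should be made because a better method is available without additional data collection, and because the analysis as worded invites either false reassurance or a misread extrapolation.

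**What to change.** Replace the adjustment with an effect-modification analysis, specified before database lock:

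1. Give each ICU its FFVM-period total fidelity score in both phases, centred at the mean across ICUs.
2. Add fidelity and intervention × fidelity to the primary GEE.
3. Report the interaction with its CI, and the RR at stated fidelity percentiles, for example the 25th and 75th.
4. Label the result as observational effect modification across ICUs. Fidelity is measured after randomisation and was not itself randomised.
5. State that an ICU with no FFVM phase has no score, and report how many are left out for this reason.

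The cost is one interaction term beyond the planned fidelity covariate and a few sentences of SAP text. The score is already planned for collection. Precision will be limited, because the interaction is estimated across only 40 ICUs; a wide CI should be reported as inconclusive, not as absence of effect modification.
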